# Ethical concerns

Patient data would be handled with utmost care not to breach patient's privacy in any form. The data would be stored in secure cabinets and/or computers which would be password-protected. To protect patient privacy, all research data would be handled in line with HA / Hospital’s policy in handling / storage / destruction of patients’ medical records. Electronic data would be saved in secured computer of the hospital with restricted access. USB Device would not be used for patient information nor personal data. Personal data (name, HKID, OPD / hospital numbers, address and any other personal identifiable information) would not be recorded on the project’s data sheets or electronic files. A study code would be used instead. The document of electronic file containing the linkage information between the study code and the identity of the patient would not contain any other information and would be kept separate from the study data files or data sheets with the same stringent security as the medical record. Any documents or electronic files containing personal identifiable information would be considered as part of the medical record and would be dealt with the same stringent regulations of security according to the hospital policies. All the investigators would be responsible for data handling and protection.

**Study Table: Masked assessment conducted at baseline and follow-up visits**

| **Assessments/number of month** | **0** | **1** | **2** | **3** | **4** | **6** | **9** | **12** | **15** |
| --- | --- | --- | --- | --- | --- | --- | --- | --- | --- |
| Assessments performed in ascending order of invasiveness | | | | | | | | | |
| **RE-VERIFY ELIGIBILITY** |  |  |  |  |  |  |  |  |  |
| **EFFICACY (SUBJECTIVE)** |  |  |  |  |  |  |  |  |  |
| Ocular Surface Disease Index **(OSDI)** |  |  |  |  |  |  |  |  |  |
| Standardized Patient Evaluation of Eye Dryness **(SPEED)** |  |  |  |  |  |  |  |  |  |
| Symptom Assessment iN Dry Eye **(SANDE)** |  |  |  |  |  |  |  |  |  |
| Ocular comfort index **(OCI)** |  |  |  |  |  |  |  |  |  |
| Dry eye questionnaire **(DEQ-5)** |  |  |  |  |  |  |  |  |  |
| **EFFICACY (OBJECTIVE)** |  |  |  |  |  |  |  |  |  |
| Non-invasive keratograph break-up time (NIKBUT) |  |  |  |  |  |  |  |  |  |
| Conjunctival bulbar hyperaemia |  |  |  |  |  |  |  |  |  |
| Tear meniscus height (TMH) |  |  |  |  |  |  |  |  |  |
| Lipid layer thickness (LLT) |  |  |  |  |  |  |  |  |  |
| Tear interferometric fringe pattern |  |  |  |  |  |  |  |  |  |
| Meiboscore (0-3) upper lid |  |  |  |  |  |  |  |  |  |
| Meiboscore (0-3) lower lid |  |  |  |  |  |  |  |  |  |
| Meibograde (0-9) upper eyelid |  |  |  |  |  |  |  |  |  |
| Meibograde (0-9) lower eyelid |  |  |  |  |  |  |  |  |  |
| Partial blinking (%) |  |  |  |  |  |  |  |  |  |
| Schirmer’s test without anesthesia (ST) |  |  |  |  |  |  |  |  |  |
| Lid margin and eyelash abnormalities (0-3) |  |  |  |  |  |  |  |  |  |
| Tear film break-up time (TFBUT)# |  |  |  |  |  | # |  |  | # |
| Corneal staining (Modified Oxford grading) |  |  |  |  |  |  |  |  |  |
| Conjunctival staining (Modified Oxford grading) |  |  |  |  |  |  |  |  |  |
| Lid wiper epitheliopathy (LWE) |  |  |  |  |  |  |  |  |  |
| Meibomiam gland expressibility (0-5) |  |  |  |  |  |  |  |  |  |
| Meibum quality (0-45) |  |  |  |  |  |  |  |  |  |
| **SAMPLE COLLECTION** |  |  |  |  |  |  |  |  |  |
| Tears sample (Schirmer’s test strip) |  |  |  |  |  |  |  |  |  |
| Conjunctival swab |  | X | X | X |  | X | X | X |  |
| Blood specimens |  | X | X | X | X | X | X | X | X |
| Expressed meibum sample A (by forceps, IPL+MGX subjects) |  |  |  |  | X | X | X | X | X |
| Expressed meibum sample B (before treatment) |  | X | X | X |  | X | X | X |  |
| **SAFETY** |  |  |  |  |  |  |  |  |  |
| Procedure-related pain (VAS)* |  |  |  |  | X | X | X | X | X |
| Visual acuity |  |  |  |  |  |  |  |  |  |
| Intraocular pressure |  |  |  |  |  |  |  |  |  |
| Lens opacity (LOCS II) |  |  |  |  |  |  |  |  |  |
| Anterior chamber activities |  |  |  |  |  |  |  |  |  |
| Iris defect/transillumination |  |  |  |  |  |  |  |  |  |
| Dilated fundus examination |  | X | X | X |  | X | X | X |  |
| Loss of lashes, eyebrows |  |  |  |  |  |  |  |  |  |
| Facial redness |  |  |  |  |  |  |  |  |  |
| Facial swelling |  |  |  |  |  |  |  |  |  |
| Facial bruises |  |  |  |  |  |  |  |  |  |
| Facial pigmentation |  |  |  |  |  |  |  |  |  |
| **EVALUATE ASSESSOR MASKING** |  |  |  |  |  |  |  |  |  |

#primary outcome

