## Methods

All measurements are conducted in accordance with the recommendations of the TFOS DEWS II Diagnostic Methodology subcommittee [22].

Participants will be assessed in a designated room at CUHK Eye Centre or CUHK Medical Centre Eye Centre with temperature of 20.3±0.5°C and relative humidity of 63±7% by the same study personnel (research assistants) masked to the treatment assignment. To minimise the impact on subsequent tests, measurements are performed in ascending order of invasiveness and are summarised in Table. The following will be measured or conducted before each treatment or follow-up visit.

Questionnaires (Traditional Chinese version)

Demographic and baseline characteristics, chronic condition, eye disease, surgery & hospitalization history, smoking & alcohol use history, life conditions, and work productivity, etc., are collected via standard questionnaires when subjects are recruited. The 12-item symptom frequency-based questionnaire Ocular Surface Disease Index **(OSDI)**, Standard Patient Evaluation of Eye Dryness **(SPEED)**, 2-item frequency- and severity-based visual analog scale Symptom Assessment iN Dry Eye **(SANDE)**, Ocular comfort index **(OCI),** and Dry eye questionnaire **(DEQ-5)** are self-administered at each study visit.

Visual acuity

Visual acuity of the participant is examined by a standard visual acuity chart as safety outcome measures.

Intraocular pressure

The intraocular pressure, the fluid pressure of the eye, is assessed by a non-contact tonometer as the safety outcome measure.

Keratograph 5M (Oculus, Wetzlar, Germany)

**Non-invasive keratograph break-up time (NIKBUT)** is measured using automated detection of first break-up, while the subject maintains fixation and is requested to refrain from blinking. Three breakup time readings are averaged in each case.

**Bulbar conjunctival hyperaemia** is evaluated according to the proprietary JENVIS grading scale from 0 to 4.

The lower **tear meniscus height (TMH)** is assessed using high magnification pre-calibrated digital imaging, and three measurements near the centre of the lower meniscus are averaged.

Lipiview II

**Lipid layer thickness (LLT)** of the tear film as determined with LipiView II (TearScience, Morrisville, NC).

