**Tear interferometric fringe pattern** is graded according to the modified Guillon-Keeler system: grade 1, open meshwork; grade 2, closed meshwork; grade 3, wave or flow; grade 4, amorphous; grade 5, colored fringes; grade 0, non-continuous layer (non-visible or abnormal colored fringes).

**Infrared meibography** is taken with the superior and inferior eyelids everted in turn. From the captured image, the proportion of meibomian glands visible within the tarsal area is graded according to the four-point meiboscore (0-3) by Arita et al. Morphological changes of meibomian glands is assessed by the ‘meibograde’ method evaluating gland distortion, gland shortening and gland dropout. Each of these characteristics is graded from 0-3, like the meiboscore, and then they are summed to give a total score of 0-9 per eyelid where a higher score represents a higher percentage of gland loss.[25]

**Partial blinking** is reported as % recorded by the Lipiview II.

Schirmer’s test (ST)

**Schirmer’s test (ST)** will be performed without anesthesia for 5 mins. The strips will be collected in sterile centrifuge tubes respectively for laboratory tests of biomarkers.

Slit-lamp biomicroscopy (to be performed by masked follow-up investigators)

**Lid margin and eyelash abnormalities**, including lid margin thickening, rounding, notching, foaming, telangiectasia, meibomian gland capping, staphylococcal lash crusting, seborrheic lash crusting, Demodex lash cylindrical collarettes, madarosis, poliosis, and trichiasis, are graded based on a four-point scale: grade 0, absent; grade 1, mild; grade 2, moderate; grade 3, severe.

Sodium fluorescein dyes are applied using the recommended technique described [21].

**Tear film break-up time (TFBUT)**, defined as the time to initial breakup of the tear film after a blink is measured three times.

**Corneal and conjunctival staining** score due to epithelial desiccation is documented according to the modified Oxford grading scheme.

**Lid wiper epitheliopathy (LWE)** is evaluated relative to Korb’s grading.

**Expressibility** of the inferior eyelid meibomian glands is assessed with the Meibomian Gland Evaluator (TearScience, North Carolina, USA) applied just inferior to the nasal, central, and temporal aspects of the eyelid margin. The proportion of meibomian orifices yielding lipid secretions is graded on a five-point scale: 0, more than 75%; 1, 50% to 75%; 2, 25% to 50%; 3, less than 25%; 4, none.

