## Study design

This is a prospective, multicentre, randomized, assessor-masked, 3-arm (1:1:1), active-controlled trial of 360 subjects with meibomian gland dysfunction contributing one study eye. For subjects with both eyes eligible, the eye with the most meibomian gland dropout (meiboscore), fewest expressible meibomian glands, thinnest lipid layer, or lowest TFBUT values (in this order) will be selected as the study eye.

Enrolled patients will be randomized into one of the following groups, 1 month after recruitment during the 15-month study period receiving bilateral treatment of:

Group A: 1-session VTP at month 0

Group B: 4-session IPL+MGX at month 0,1,2,3

Group C: twice daily EW for 15 months

The study will be conducted in accordance with the tenets of the Declaration of Helsinki, and the protocol will be sent for approval by the research ethics review committee of each participating hospital. All participants will provide written informed consent before participation. Study will be registered at ClinicalTrials.gov prior to recruitment. The baseline, follow-up assessments and study procedures will be conducted as described above. Participants will be given contact of the study team to report adverse events at any time, which will also be actively sought at each follow-up visit. Additional follow-up appointment will be provided as and when required.

Recruitment, baseline and follow-up assessment and tear substitutes

Patients will be washed out for 1 month and maintained on one single topical lubricant to be used as frequently as needed from recruitment to study exit (total 16 months). Cool Eye eye drops- hypromellose (3 mg/ml) containing 0.0002 ml of 50% Benzalkonium Chloride solution as preservative will be provided by the research team.

Clinical evaluations are done according to the recommendations of the TFOS DEWS II diagnostic methodology subcommittee at month -1 (recruitment), 0 (baseline), 1, 2, 3, 4, 6, 9, 12, 15 (total 10 visits). Examination is conducted on both eyes starting on the study eye. To minimize the impact on ocular surface and tear film physiology, tests are done from least to most invasive at each follow-up and/or prior to each treatment.

Randomization, masking of assessors

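### The listed test order puts the 5-minute Schirmer test before TFBUT, the primary outcome, with no recovery interval, and leaves the running order unclear

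*Protocol*

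**What the plan says.** The ordering rule appears three times in the Protocol.

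- Methods: "measurements are performed in ascending order of invasiveness and are summarised in Table".
- Study design, paragraph on recruitment and follow-up assessment: "tests are done from least to most invasive at each follow-up and/or prior to each treatment". The reason given is "To minimize the impact on ocular surface and tear film physiology".
- Study Table, first line: "Assessments performed in ascending order of invasiveness".

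Two places give an actual sequence.

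- In Methods, Schirmer's test "will be performed without anesthesia for 5 mins". The slit-lamp block comes after it: lid margin and lash grading, then dye ("Sodium fluorescein dyes are applied using the recommended technique described"), TFBUT, staining and lid wiper grading.
- In the Study Table, the row "Schirmer’s test without anesthesia (ST") stands two rows above "Tear film break-up time (TFBUT"). Only lid margin and eyelash grading lies between them.

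The same table has a further row for the tear sample on the Schirmer strip, under sample collection, below TFBUT, staining and meibum quality. The data analysis section names TFBUT at months 6 and 15 as the primary outcome, and TFBUT of 5 seconds or less is an inclusion criterion. No section sets a time between removing the strip and instilling the dye.

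**The concern.** A paper strip left for 5 minutes in an unanaesthetised eye absorbs tears, touches the ocular surface and provokes reflex tearing. TFBUT measures the stability of that same tear film. If the listed order is followed, the primary endpoint and the staining scores are read shortly after the test most likely to alter them, and in the study eye, because examination starts there. The ordering rule exists to prevent this.

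With no interval fixed, the time from strip to TFBUT can also differ between visits, assessors and centres. That adds variability to the primary outcome which a worksheet could remove. The TFBUT values may also be less comparable with the published ones behind the sample size. Because the table shows the strip both before and after TFBUT, different sites could reasonably run different orders.

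**Working it through.** **Order against rule**

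| Source | What it gives | Schirmer relative to TFBUT |
|---|---|---|
| Methods, opening paragraph | Rule, pointing to the table | – |
| Methods, test descriptions | Sequence | Before |
| Study design | Rule and its purpose | – |
| Study Table, efficacy rows | Rule in first line, then sequence | Before (two rows above) |
| Study Table, sample rows | Strip listed again | After |

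Methods and the efficacy rows agree, so the order does not come from a broken table. The sample-collection row is what makes the running order ambiguous.

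**Possible size**

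The plan has no figure for this effect, so there is none to reproduce. The calculation below shows only what an assumed amount of noise would do.

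Inputs from the sample size section:
- Differences in TFBUT change: 1.9 s for VTP and 3.3 s for IPL+MGX.
- SDs: 4.04 for VTP, 1.88 for IPL+MGX, and 3 as the planning average.
- Type I error 2.5%, taken as two-sided because all tests are stated to be two-tailed.
- 120 per group with 35% drop-out, so completers per arm = 120 × 0.65 = 78.

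Assumption: the prior Schirmer test adds independent noise with SD s = 1, 1.5 or 2 s to the change in TFBUT. The documents do not supply s.

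Formulas:
- Inflated SD = √(SD² + s²).
- Noncentrality = difference / (inflated SD × √(2/78)).
- Power from the noncentral t distribution with 2 × 78 − 2 = 154 degrees of freedom; critical value 2.26.

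Worked case (1.9 s, SD 4.04, s = 2): inflated SD = √(16.32 + 4) = 4.51; noncentrality = 1.9 / (4.51 × 0.160) = 2.63; power 64%.

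| Contrast | s = 0 | s = 1 | s = 1.5 | s = 2 |
|---|---|---|---|---|
| VTP vs EW, 1.9 s, SD 4.04: inflated SD | 4.04 | 4.16 | 4.31 | 4.51 |
| Power | 75% | 72% | 69% | 64% |
| VTP vs EW, 1.9 s, SD 3: inflated SD | 3.00 | 3.16 | 3.35 | 3.61 |
| Power | 95% | 93% | 90% | 85% |
| IPL+MGX vs EW, 3.3 s, SD 1.88 or 3: power | about 100% | about 100% | about 100% | about 100% |

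With s = 0.5 s, the loss in the first VTP case is about 1 point.

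A difference of 1.4 s (3.3 − 1.9) is not used. It contrasts IPL+MGX with VTP, whereas the protocol says the trial is powered for each of them against EW.

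**The case against.** The strongest objections, and what stands of each:

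- **The protocol never ranks the two tests.** Correct. That a 5-minute strip disturbs the tear film more than dye instillation is general clinical knowledge, and the diagnostic report the protocol follows is not at hand. A reader might infer a proven breach of the ordering rule. The documents support less: the listed order sits badly with the rule's stated purpose.
- **The table is grouped by domain, so it is not a running order.** Partly correct. Visual acuity and tonometry come last in the table but early in Methods. However, Methods also puts Schirmer before TFBUT, and the table presents itself as the order of testing. This objection strengthens the case for stating the order.
- **Time does pass between the tests.** Methods places the grading of 12 lid and lash signs between them. That is some delay, but not a fixed or stated one.
- **The noise SD is invented and may be counted twice.** Both parts stand. The range of 1 to 2 s is assumed. If the cited studies also ran Schirmer first, their SDs already contain the noise.
- **No bias follows.** Correct. A reader might infer that the order biases the comparison or draws the arms together. The order is the same in all arms and at baseline, and assessors are masked. Independent noise widens the SD but does not shrink the mean difference. Attenuation is conceivable but not shown.
- **Schirmer is itself an objective efficacy measure, and strips may need to be free of dye.** This stands as a real trade-off, although the dye reason is inferred and not stated. It is why the fix offers an alternative.

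**Conclusion.** The point holds as a cheap improvement to how the primary endpoint is measured. Both listed sequences put a 5-minute unanaesthetised Schirmer test before TFBUT and staining, no interval is fixed, and the repeated strip row leaves the actual order open.

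The likely consequence is avoidable, non-differential noise in TFBUT. Its size cannot be derived from the documents. Under an assumed noise SD of 1 to 2 s, the VTP-versus-EW comparison loses about 3 to 11 points of power at SD 4.04 and about 2 to 11 points at the planning SD of 3. The IPL+MGX comparison loses almost nothing. These losses rest on three assumptions: the noise is independent, 78 patients per arm complete, and the published SDs do not already include it.

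It would go too far to say that the endpoint will certainly be read on a disturbed tear film, or that the treatment comparison is invalid.

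**What to change.** In the Methods test descriptions and the Study Table, state one running order that applies at every visit, to both eyes and in all arms, with TFBUT and staining before Schirmer's test. Reconcile the two Schirmer rows in the table so that the time of strip collection is unambiguous.

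If dye-free strips are essential, keep Schirmer first, say why, and fix one minimum interval between strip removal and fluorescein instillation, identical at every visit and in every arm.

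Two alternatives should be avoided. Reordering only at months 0, 6 and 15 would make TFBUT and Schirmer values non-comparable across visits and weaken the objective on the 15-month course. Taking strips first from the fellow eye would conflict with the Study design rule that examination starts on the study eye.

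The cost is a revised visit worksheet. The downside is that strips may carry dye and the Schirmer value then follows dye instillation or, under the second option, that each visit lengthens by the interval. Neither option changes treatment or sample size.

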**Study Flow Chart**

| **Continue standard topical lubricant**  **monotherapy during study period** | **Month (-1)** | **Patient recruitment and randomization (1:1:1)** | | |
| --- | --- | --- | --- | --- |
|  |  | **4-week washout with standard topical lubricant monotherapy** | | |
|  |  | **Group A** | **Group B** | **Group C** |
|  | **Month 0** | **1-session**  **vectored thermal pulsation** | **4 monthly intense pulsed light and meibomian gland expression** | **Twice-daily eyelid hygiene warm compress** |
|  | **Month 1** |  |  |  |
|  | **Month 2** |  |  |  |
|  | **Month 3** |  |  |  |
|  | **Month 4** |  |  |  |
|  |  |  |  |  |
|  | **Month 6** |  |  |  |
|  |  |  |  |  |
|  |  |  |  |  |
|  | **Month 9** |  |  |  |
|  |  |  |  |  |
|  |  |  |  |  |
|  | **Month 12** |  |  |  |
|  |  |  |  |  |
|  |  |  |  |  |
|  | **Month 15** |  |  |  |
